### Economic analysis

Severe sprains may have a range of direct cost consequences across primary and secondary health care, they may also have cost consequences for patients themselves in terms of their personal expenditure and return to work. The costing study will seek to adopt a broader societal perspective, including patient costs, when estimating differences in the cost of resources used in the four arms of the trial. The economic analysis will compare resource use (costs) with any measurable changes in health outcomes (benefits). The health outcomes of the four technologies will be measured in terms of changes in specific disease parameters and validated measures of health-related quality of life (HRQL). Any uncertainties in the cost and outcomes data will be incorporated into a sensitivity analysis.

The cost of each mechanical support protocol will be determined through observation and will include staff time, overheads, equipment and transport; plus follow-up visits to hospital, GP surgeries, physiotherapists or others. The consequences for patients in terms of GP and hospital visits, including travel expenses and time off work, and expenditure on aids or private practitioner input are obtained from structured resource use questions added to patient follow-up questionnaires. Further treatments recorded include pain relieving medications, anti-inflammatory and other topical agents, bandages, supports or footwear. Patients are also asked to distinguish whether these are NHS-funded or private treatment paid for by the individual or private provider. Patient self-reported information on service use has been shown to be accurate in terms of intensity of use of different services [20]. Hospital notes and records will also be audited for information on service use. The cost of primary and hospital services will be estimated from a variety of sources, including the finance departments of the trial hospitals and services concerned and national sources [21,22]. Differences in resource use and outcomes are ascertained in follow-up questionnaires at 12 weeks and 9 months.

The appropriate technique of economic evaluation will depend on the results of the study [23]. The simplest eventuality would be where the least expensive intervention is found to be better on at least one outcome measure and no worse on any other i.e. dominant. Another is where two interventions have the same outcomes in which case cost-minimisation analysis will be used to compare the two. However, where an intervention is clearly better in terms of outcome but is also more costly, a different approach is required. One accepted method is to compare the different interventions in terms a single outcome measure identified as clinically important for the condition being treated. The primary outcome meets this requirement. Therefore, the costs per unit improvement in mobility will be used to provide an estimate of overall cost-effectiveness; average and incremental (relative to reference treatment) cost-effectiveness ratios will be estimate for the different treatments used. However, this approach does not allow comparison with other types of intervention/condition combinations and also does not consider the value (utility) of differences in improvement in health status. In the present study, the EQ-5D will be used to generate such utility scores that can be compared to costs. A cost-utility analysis will estimate outcomes in terms of differences in quality-adjusted life years (QALYs), representing the period of life subsequent to a health care intervention weighted or adjusted for the quality of life experienced by the patient during that period, and compare these with cost for the four interventions [23]. The cost-utility analysis will present the incremental cost of the extra benefit gained both in summary form in terms of incremental cost per QALY, and also using a 'disaggregated' approach where the extra costs are presented alongside the HRQOL dimensions such as pain.

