### Data analyses

The analysis will be conducted as intention to treat. An analysis of all people who completed the trial will be undertaken, and in addition, a sensitivity analysis will be undertaken to assess the range of potential biases that could result from loss to follow up or withdrawal. Numerical and graphical summaries of all the data will be compiled, including a detailed description of missing data at the clinic visit, questionnaire and individual level.

Logistic and log-linear multinomial regression models will be used to provide estimates of the recovery rates and the prevalence of residual symptoms, with confidence intervals. As there are multiple centres and repeat assessment, random effect (or hierarchical) models will be used to investigate the components of variation. The common current and cheapest therapy is Tubigrip^®^, so each of the three other treatments will first be compared with it. Any treatments found to be more effective than Tubigrip^® ^will be compared with each other. Regression modelling will allow an assessment of factors that might indicate the appropriate choice of treatment. As these analyses are pre-specified, issues of multiple comparisons are minimal.

The sensitivity of the above analyses to missing data at various levels will be assessed and quantified using modern statistical methods for incomplete multivariate data [19].

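### The economic method is chosen by the trial's results, and cost-minimisation is triggered by outcomes being the same with no criterion for sameness

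*Protocol article*

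**What the plan says.** The relevant text is in the Economic analysis section of the protocol article. The general rule is: "The appropriate technique of economic evaluation will depend on the results of the study". Three branches follow.

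- **Dominance:** the case where "the least expensive intervention is found to be better on at least one outcome measure and no worse on any other i.e. dominant".
- **Cost-minimisation:** "Another is where two interventions have the same outcomes in which case cost-minimisation analysis will be used to compare the two".
- **Ratio methods:** "where an intervention is clearly better in terms of outcome but is also more costly, a different approach is required". The text then describes cost per unit improvement in mobility, with average and incremental ratios.

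The same section goes on to an EQ-5D cost-utility analysis that will estimate QALY differences and "compare these with cost for the four interventions". Earlier it promises: "Any uncertainties in the cost and outcomes data will be incorporated into a sensitivity analysis".

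On design, Sample size describes a two-sample t-test at the 0.05 level, an MCID of 10 percent, power above 90% for that difference on the primary outcomes, a target of 600–650 participants, and a 20% inflation for loss. Data analyses compares each support with Tubigrip and carries forward those found more effective.

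**The concern.** Cost-minimisation takes the difference in effect to be zero and compares costs alone. That is defensible only with evidence that the effects are equivalent. The article sets out a superiority design and never links its MCID to the economic rule. Estimates from two arms will almost never be equal, so someone must decide, after seeing the results, what counts as the same. The decision tool nearest to hand is the superiority test, and failing that test is not evidence of equivalence.

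The dominance branch shares the weakness. Being no worse must be judged over the several measures in Table 1, again without a margin. The threshold of being clearly better in the third branch is also undefined.

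Measuring the cost of each strategy is the second of the trial's two stated aims. If the rule is followed on that reading, an arm with a worthwhile but non-significant benefit is compared on cost only, and the uncertainty about its effect drops out of the economic conclusion.

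**Working it through.** **Inputs from Sample size:** 0.05 level, MCID 10 percent, power above 90%, 600–650 participants, 20% inflation. The eligibility text gives four arms.

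**Assumptions:** equal allocation, a two-sided test, normal approximation, power of exactly 90% at the MCID. The SD is not stated. Points are used only if 10 percent is read as 10 points.

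**1. The plan's own sample size.** It cannot be reproduced without the SD, only checked for plausibility. With an MCID of 0.40 SD:
- n per arm = 2 × ((1.960 + 1.282) / 0.40)² ≈ 131.3, so 132
- four arms: 528
- with 20% added: 528 × 1.2 ≈ 634; with 20% lost: 528 / 0.8 = 660

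This fits 600–650 and the description of a small to moderate effect.

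**2. Evaluable numbers.** 600/4 × 0.8 = 120 and 650/4 × 0.8 = 130 per arm. The MCID giving 90% power is 3.242 × √(2/n), which is 0.418 SD at n = 120 and 0.402 SD at n = 130. If the MCID is 10 points, the SD is 10/0.418 = 23.9 to 10/0.402 = 24.9 points.

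**3. How often a real benefit is non-significant.** With 90% power at the MCID, the MCID equals 3.242 standard errors whatever n and SD are. For a true benefit of f × MCID:

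P(non-significant) ≈ 1 − Φ(3.242 f − 1.960)

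| True benefit | 3.242 f − 1.960 | P(non-significant) |
|---|---|---|
| 0.50 MCID | −0.339 | 63% |
| 0.70 MCID | 0.309 | 38% |
| 0.75 MCID | 0.471 | 32% |
| 1.00 MCID | 1.282 | 10% |

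**4. Width of the interval.** The 95% half-width is 1.960 / 3.242 = 0.605 of the MCID, about 6 points on the points reading. An observed benefit of half the MCID would have an interval from 0.50 − 0.605 = −0.105 to 0.50 + 0.605 = 1.105 MCID. That is non-significant, yet it includes the full MCID.

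**5. Sensitivity to the power.** The article says above 90%. With an MCID of 0.40 SD and all 162.5 per arm evaluable, power is 95%. The MCID is then 0.40 × √(162.5/2) = 3.606 standard errors. Half the MCID is non-significant with probability 1 − Φ(1.803 − 1.960) ≈ 56%, and the half-width is 1.960 / 3.606 = 54% of the MCID.

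**6. Could this trial show equivalence if a margin were set?** Take the MCID as margin, assumed 0.40 SD, with a true difference of zero. Power of two one-sided tests = 2Φ(0.40/SE − z) − 1, with SE = √(2/n) in SD units.
- One-sided 0.05 (z = 1.645): n = 120 gives 2Φ(3.098 − 1.645) − 1 = 85%; n = 130 gives 2Φ(3.225 − 1.645) − 1 = 89%.
- One-sided 0.025 (z = 1.960): 75% and 79%.

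So the numbers could support a claim of equivalence against a margin of that size. The margin itself is missing.

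**7. The text against itself.** The opening rule makes the technique conditional on results. The cost-utility sentences name all four interventions and carry no condition of their own, but they follow the branch for an arm that is better and more costly. Both readings are open, and they lead to different analyses.

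**The case against.** The strongest reply is that the harm is inferred. The article names no test or p-value for sameness, and the cost-utility analysis is described for all four arms. On an unconditional reading, QALY differences are estimated whatever the clinical test shows and nothing is lost. This stands as far as it goes: a reader might infer that the plan is certain to discard benefit, and the text does not support that. But the unconditional reading contradicts the opening rule and the commitment to cost-minimisation, so the text still needs reconciling. An undefined trigger applied once results are known is itself a defect.

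Three other strong readings are tempting and should not be made.

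- **That cost-minimisation automatically favours Tubigrip.** The article calls Tubigrip the cheapest therapy, but the costing is societal and includes further visits, patient spending and time off work. Another arm could have the lowest total.
- **That the trial cannot show sameness.** An interval of about ±6 points around zero lies inside ±10. The lack is of a stated margin, not necessarily of patients.
- **That uncertainty is ignored throughout.** A sensitivity analysis for cost and outcome data is promised, and its methods may fairly be left to a fuller document. But nothing in the text says it would bring back an effect that the cost-minimisation branch has taken to be zero.

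It is also fair that the percentages describe a t-test on the mobility outcome, not QALYs, and are not the frequency with which cost-minimisation would be invoked.

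**Conclusion.** The point holds as a defect in a stated rule, not as a missing detail. The economic method is chosen after the results are seen, and one branch removes the effect from the comparison on a condition that the article does not define. If the condition is read as non-significance, a true benefit of half the MCID would meet it about 63% of the time at 90% power, or about 56% at 95%. The result could still be compatible with a benefit as large as the MCID. These figures rest on equal arms, a two-sided 5% test and the primary outcome; the point values also read 10 percent as 10 points. In that branch the conclusion favours the arm with the lowest total societal cost, whichever it is, and leaves out the uncertainty in effect. The economic conclusion is affected; the primary clinical analysis is not.

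**What to change.** In Economic analysis:

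1. Remove the sentence that makes the technique depend on the results.
2. State that the EQ-5D cost-utility analysis (incremental cost per QALY) and the planned cost per unit of mobility are carried out for all four arms whatever the clinical result.
3. Base both on estimated mean differences in cost and effect with their joint uncertainty, for example by bootstrap with an acceptability curve.
4. Judge dominance on those estimates, not on a series of comparisons across outcome measures.
5. Delete cost-minimisation, or restrict it to the case where equivalence is shown against a margin stated in advance for a named outcome and time point.

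The EQ-5D and resource-use data are already planned. The cost is a change of wording and slightly more analysis work, with no change to recruitment or follow-up.

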Practice has been gradually changing from immobilisation of the injured joint to early mobilisation. To aid mobilisation the use of mechanical supports has been suggested. These supports vary in the amount of ankle movement they allow, but all encourage ankle flexion/extension and aim to minimise inversion/eversion that theoretically reduces the risk of further ligament injury. Movement is also proposed as a way of retraining the ankle proprioception which may reduce recurrent injury rate [9]. Other hypothesised benefits of mechanical supports are early restoration of functional mobility, rapid return to usual activities, reduction of pain because the joint is stabilised and protected, and improved quality of life. However, there is also the possibility of discomfort and inconvenience owing to restriction of joint range, and delayed healing, skin and circulatory problems.

The present study has two aims

1. To estimate the clinical effectiveness of three different methods of mechanical support (below knee cast, Aircast^® ^ankle support and Bledsoe^® ^boot) in comparison to Tubigrip^® ^in

a. The recovery of mobility (primary outcome)

b. The recovery of usual occupation

c. Avoidance of residual symptoms including recurrent instability, lasting limitation of physical activity, and need for further medical, rehabilitation or surgical treatment.

2. To measure the cost of each strategy, including treatment and subsequent health care costs.

The NHS National Co-ordinating Centre for Health Technology Assessment has guided the selection of treatments. Tubigrip^® ^has been chosen as the reference treatment because it is the cheapest and one of the most commonly used [10]. The Bledsoe^® ^boot is lightweight and incorporates a novel design to promote ease of walking. However it is considerably more expensive, and it's clinical and cost effectiveness is yet to be proven. The below knee cast is Scotch^® ^Cast is commonly used for casting in the NHS [9]. There is a range of lightweight mechanical supports available, and we have selected the Aircast^® ^Brace.

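### The planned cost-per-mobility ratios are each taken against Tubigrip, or against nothing, so they can hide a poor last step to a costlier support

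*Protocol article*

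**What the plan says.** The Economic analysis section of the protocol article sets out to cost all four strategies, "estimating differences in the cost of resources used in the four arms of the trial". Where one treatment is better but dearer, it says that "the costs per unit improvement in mobility will be used to provide an estimate of overall cost-effectiveness", and then that "average and incremental (relative to reference treatment) cost-effectiveness ratios will be estimate for the different treatments used".

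The reference is identified in the Background section: Tubigrip "has been chosen as the reference treatment because it is the cheapest and one of the most commonly used". The same section says of the Bledsoe boot: "However it is considerably more expensive, and it's clinical and cost effectiveness is yet to be proven".

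For QALYs the wording differs: "The cost-utility analysis will present the incremental cost of the extra benefit gained both in summary form in terms of incremental cost per QALY". No comparator is given there.

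The Data analyses section says that treatments found more effective than Tubigrip "will be compared with each other". That sentence belongs to the clinical effectiveness analysis.

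**The concern.** A patient receives one of the four treatments, so the options are mutually exclusive. The question for each option is what its extra effect costs over the best cheaper option, which need not be the cheapest option of all. If every incremental ratio is taken against Tubigrip, a dear support is credited with gains that a cheaper support would have delivered.

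An average ratio divides one arm's cost by its own effect. It implicitly compares the arm with zero cost and zero effect, which nobody is choosing.

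The trial has three supports against one reference, and one support is described in advance as much dearer. A common-reference ratio could mislead in exactly that setting. At stake is the economic message about which support, if any, is worth its cost.

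**Working it through.** **The plan's own figure.** There is none to reproduce. The article states no cost, effect, threshold or ratio. The check is therefore algebraic, with assumed inputs.

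**Formulas.** C is mean cost and E is mean effect.
- Average ratio: C_i / E_i.
- Ratio against the reference: (C_i − C_ref) / (E_i − E_ref).
- Sequential ratio: (C_i − C_next) / (E_i − E_next), where next is the next less costly option that remains after dominated and extendedly dominated options are removed.

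**Assumed inputs (none from the article).** Costs are in arbitrary currency units and mobility is in points.

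| Arm | Cost | Mobility | Average ratio | Against Tubigrip | Against next option |
|---|---|---|---|---|---|
| Tubigrip | 100 | 60 | 100/60 = 1.67 | – | – |
| Cast | 130 | 66 | 130/66 = 1.97 | 30/6 = 5.00 | 30/6 = 5.00 |
| Aircast brace | 150 | 69 | 150/69 = 2.17 | 50/9 = 5.56 | 20/3 = 6.67 |
| Bledsoe boot | 300 | 70 | 300/70 = 4.29 | 200/10 = 20.0 | 150/1 = 150 |

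The sequential ratios rise (5.00, 6.67, 150), so no arm is extendedly dominated and the brace is the proper comparator for the boot.

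**Why the two ratios differ.** The ratio against Tubigrip is an average of the steps, weighted by the effect gained at each step. For the boot it is (6/10) × 5.00 + (3/10) × 6.67 + (1/10) × 150 = 3 + 2 + 15 = 20. The last step costs 150/20 = 7.5 times as much per point as the ratio that the plan would report.

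**Effect on the choice.** At an assumed value of 25 per mobility point, incremental net benefit over Tubigrip is:
- cast: 25 × 6 − 30 = 120;
- brace: 25 × 9 − 50 = 175;
- boot: 25 × 10 − 200 = 50.

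The boot passes against Tubigrip (20 is below 25), yet the brace is the better choice.

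**Range.** Keep the brace at +50 cost and +9 points over Tubigrip, and the value at 25 per point. The boot passes against Tubigrip when its gain exceeds (C − 100)/25. It is still worse than the brace while its gain is below 9 + (C − 150)/25.

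| Boot cost C | Passes against Tubigrip above | Worse than brace below |
|---|---|---|
| 200 | 4 points | 11 points |
| 250 | 6 points | 13 points |
| 300 | 8 points | 15 points |

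The effect does not depend on one chosen set of numbers. Outside these ranges it does not arise.

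**Average ratios.** In the example they run 1.67, 1.97, 2.17, 4.29. They simply favour the cheapest arm and say nothing about whether a further point is worth its cost.

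**QALYs, only if the same comparator were used.** Assume the same costs and QALYs of 0.5000, 0.5060, 0.5090 and 0.5115 (Tubigrip, cast, brace, boot). The boot then costs 200/0.0115 = 17,391 per QALY against Tubigrip and 150/0.0025 = 60,000 against the brace.

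**The case against.** The strongest reply is that the economic plan is conditional and not confined to Tubigrip. The section says that the technique depends on the results. It recognises dominance by the least expensive option, and it allows two interventions with equal outcomes to be compared on cost alone. If brace and boot differed trivially, that last route would favour the cheaper one. Supports that beat Tubigrip are compared with each other in the clinical analysis, and cost and outcome uncertainty goes into a sensitivity analysis. A reader given each arm's costs and effects could also obtain sequential ratios by subtraction.

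Only part of this stands. The cost-minimisation route needs equal outcomes, the dominance wording does not reach dominance among the supports, the support-versus-support comparison is clinical, and a sensitivity analysis does not change the comparator. Where a support is better and dearer, the stated ratio is the one against Tubigrip.

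Three stronger readings are tempting but not supported:
- *All incremental ratios are against Tubigrip.* This is explicit only for cost per unit of mobility. Extending it to cost per QALY is inference.
- *Average ratios also flatter the costliest support.* They are uninformative, but they usually point the other way.
- *The plan will rank the supports wrongly.* The article sets no ranking rule, adoption rule or threshold, and gives no data to show that the pattern will occur.

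The absence of acceptability curves is also no fault, since an article may leave that to the full protocol.

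**Conclusion.** The point holds for the cost-per-mobility analysis. The comparator is a stated choice, not a detail left to a fuller document, and it is the wrong one for four mutually exclusive options. It can make a costly support look acceptable when a cheaper one already gives most of the gain.

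The size cannot be taken from the article. The 20 against 150 per point in the illustration rests entirely on assumed costs and effects, and the problem needs an effective, cheaper middle option. If no support improves on Tubigrip, it does not arise. For QALYs the fault is narrower: the comparator is left unnamed and should be stated. The clinical analysis, the design and the data collection are unaffected. The text should be changed, but the trial's main result does not depend on it.

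**What to change.** In the Economic analysis section, replace the planned ratios with a full incremental analysis:
- order the four arms by observed mean cost;
- remove dominated and extendedly dominated options;
- report each remaining incremental ratio against the next less costly remaining option, or report net benefit for all four arms jointly;
- drop the average ratios;
- state the same comparator rule for cost per QALY.

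The cost is a change of wording and a little more analysis on the same data. Nothing further has to be collected.
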